#### Process evaluation

With the exception of the behavioural change, each topic of the process evaluation will be reported descriptively on the company level and on the individual level. The items of the behavioural change will be pre-post tested using a General Linear Mixed Model. IBM SPSS Statistics 20 will be used for the statistical tests.

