### Study design

A randomised intervention trial with a follow-up at six months is performed to compare the effectiveness of the two ergonomic guidance strategies, a face-to-face guidance strategy and an e-guidance strategy, of a PE intervention. The effectiveness of both guidance strategies will be compared on the use of ergonomic measures, work ability, physical functioning, limitations due to physical problems of individual construction workers, a process evaluation and a cost-benefit evaluation.

According to the researchers, the study protocol did not met the criteria of the “Act medical-scientific research with human participants” and therefore, the Medical Ethics Committee of the Academic Medical Center Amsterdam (AMC) was not asked for approval of the study protocol.

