First of all, the knowledge of the relationship between ergonomic measures, physical work demands and musculoskeletal disorders will be asked through two statements. An example of a statement is: “Due to long and frequent lifting and bending, I have an increased risk of low back pain. This can be reduced by using a raised hod”. The statements will be adapted for the different occupations, and construction workers will be asked if they agree with the statement. They can answer with a ‘yes’ , ‘no’ or ‘I don’t know’. Knowledge will be rated as good when both questions are answered affirmatively, and knowledge within a construction company is defined as good when the knowledge of 75% of all the construction workers within the company is rated as good.

The attitude of the construction workers towards working with ergonomic measures is asked with five yes or no items, such as “I only use ergonomic measures when I have physical complaints”, and is defined as good when four of the five items are scored positively. On the company level, attitude is considered good when at least 75% of the construction workers scored positively.

The motivation to work with ergonomic measures is asked through a single yes or no question. This question is: “When your employer provides ergonomic measures, are you willing to use them?” If the question is answered in the affirmative, construction workers are considered to have the motivation to work with ergonomic measures. Motivation is considered as good at company level when at least 75% of the construction workers answered the question in the affirmative.

Of the four earlier defined clusters of ergonomic measures, the ability to use these ergonomic measures will be asked. For each cluster, construction workers can assess their ability as good or poor.

As with the ability to use, the facilitation of each of four clusters of ergonomic measures will be assessed. In addition, a question is asked concerning whether the construction company has set up rules or procedures for the use of ergonomic measures.

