### Statistical analyses

#### Effect evaluation

Descriptive variables, primary and secondary outcome measures at baseline and after six months will be presented for the two guidance strategies per construction company using descriptive statistics. Differences in descriptive variables between the two guidance strategies will be tested using an independent samples *t*-test for continuous data or a Chi-square test for proportions.

The results of the primary and secondary outcome measures on the individual worker level may be influenced by the dependency of the company in which an individual worker is working. To correct for this dependency, the statistical analyses of the outcome measures to test differences between baseline and after six months for both guidance strategies will be done using a Generalized Linear Mixed Model. IBM SPSS Statistics 20 will be used for the statistical tests.

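### The behavioural-change items are tested only before against after, with a normal-theory model for mostly binary items, so the planned test cannot compare the two guidance strategies

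*Protocol article*

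**What the plan says.** In the protocol article, Statistical analyses, Process evaluation, every process topic except behavioural change is reported descriptively. For behavioural change the text is: "The items of the behavioural change will be pre-post tested using a General Linear Mixed Model". It names no strategy term.

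The items are defined under Outcome measures, Process evaluation:

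- Knowledge: "Knowledge will be rated as good when both questions are answered affirmatively".
- Attitude: "The attitude of the construction workers towards working with ergonomic measures is asked with five yes or no items", rated good when four of the five are positive.
- Motivation: "The motivation to work with ergonomic measures is asked through a single yes or no question".
- Ability, for each cluster of measures: "construction workers can assess their ability as good or poor".
- Culture: positive for a worker when all three items are affirmed.
- Facilitation: no response format is stated.

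For the primary and secondary outcomes, Statistical analyses, Effect evaluation names the other model family: the analysis of differences between baseline and six months "for both guidance strategies will be done using a Generalized Linear Mixed Model".

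Study design lists what the two strategies will be compared on, and the list ends with "limitations due to physical problems of individual construction workers, a process evaluation and a cost-benefit evaluation". Outcome measures, Process evaluation makes behavioural change one of the process indicators. Limitations says that the interest lies in the guidance strategies, not in the participatory ergonomics intervention itself, and acknowledges that there is no control group.

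**The concern.** Both arms receive the participatory ergonomics intervention, and only the mode of guidance is randomised. The comparison that randomisation protects is therefore face-to-face against e-guidance. A before-after test does not use it, whichever way it is run:

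- **Pooled over arms**, it shows a change over six months that cannot be separated from other changes over time, because no arm is untreated.
- **Run within each arm**, it gives two p-values, and readers will be drawn to compare them. One significant and one non-significant result is not evidence that the arms differ.

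Behavioural change is also the pathway through which the Background section expects guidance to act, so a wrong statement about which strategy moved it would affect how the trial is interpreted.

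The second issue is model family. A General Linear Mixed Model assumes normal errors of constant variance. Yes/no items have a variance that depends on the proportion, and their effects are usually expressed as odds ratios.

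**Working it through.** **Inputs from the Sample size section.** ICC 0.01, on average 25 workers per company, six companies per group, and 80% power (for the primary outcome only). The design effect reproduces: 1 + (25 − 1) × 0.01 = 1.24. So does the adjusted size: 113 × 1.24 = 140.1, stated as 140. Six companies of 25 give 150 workers per arm. The protocol article gives no figure for the behavioural items, so everything below is illustration under stated assumptions.

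**1. Separate tests per arm.** Assume the same true change and the same power *p* in both arms, with independent arms. The chance that exactly one arm is significant is 2*p*(1 − *p*):

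- *p* = 0.50: 2 × 0.50 × 0.50 = 50%
- *p* = 0.80: 2 × 0.80 × 0.20 = 32%
- *p* = 0.90: 2 × 0.90 × 0.10 = 18%

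Power for these items is not stated; 80% is borrowed from the primary outcome.

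**2. Interval for the change under each variance model.** Assume an item moves from 75% to 95% in 150 workers with design effect 1.24, ignoring within-worker correlation. The binomial variances are 0.75 × 0.25 = 0.1875 and 0.95 × 0.05 = 0.0475, with mean 0.1175.

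- Binomial: 1.96 × √((0.1875 + 0.0475) × 1.24/150) = ±8.6 points
- Constant variance: 1.96 × √(2 × 0.1175 × 1.24/150) = ±8.6 points

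They are identical because the pooled variance is the mean of the two and the numbers at each time are equal.

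**3. Type I error of a linear before-after test.** This was simulated with 4,000 replicates of 150 workers in six companies, random-effect SDs on the logit scale of 1 (worker) and 0.18 (company), and no dropout. The test was a normal test on within-worker differences. Rejection under no change was 4.9%, 5.3% and 4.8% at baselines of 50%, 90% and 97%. The company effect was held constant over time, so the check does not cover companies drifting apart.

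**4. Scale, once a strategy contrast is added.** A 10-point rise is a log odds ratio of 0.41 from 50% to 60% but 1.21 from 85% to 95%. With the same odds ratio in both arms (log odds ratio 1.0), a linear strategy-by-time test rejected in:

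- 4.6% of simulations with both baselines at 50%
- 7% with baselines of 50% and 65%
- 34% with baselines of 50% and 85%

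In the last two cases the risk differences really do differ. The figures show only that the effect scale has to be chosen in advance.

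**The case against.** The strongest reply is that the before-after test suits the stated purpose. The article expects the interventions to change workers' behaviour and measures it twice for that reason, and the Abstract gives the process evaluation the aim of finding barriers and facilitators for both strategies. The comparison promised in Study design also covers the cost-benefit evaluation, which is only described, so it does not promise a test for every component. A strategy term could sit in a fuller document. This lowers the severity. It does not remove the point: for the one indicator that is tested, the article fixes the test, and the test fixed is not the comparison of interest.

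A reader might also infer that the linear model makes the planned test invalid, with wrong error bars for items near 100%. The documents do not support that. The tested quantity is the change; its interval is the same under both variance models in the illustration, and type I error stays near 5%. Intervals for the level at a single time would differ, but the section does not say that such intervals will be reported.

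A reader might further infer that the two analysis sections contradict each other. They cover different variables, so different models are not in themselves a contradiction. What stands is that *General* does not match the response formats, whether it is a slip or deliberate. A 0–5 attitude sum could be treated as roughly continuous, but the text says that the items are tested.

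**Conclusion.** The point holds, at minor to moderate severity. The main fault is the contrast: as written, the analysis cannot show whether one strategy changed behaviour more than the other. Separate tests per arm would give a split result about 32% of the time with equal true effects at 80% power (18% to 50% for power from 90% down to 50%). The mismatch between a normal-theory model and mostly binary items is secondary and may be only a wording slip; it is not shown to damage the before-after p-value. The conclusion rests on reading the sentence as it stands, with no strategy term, and on assumed rates and power for items for which the document gives none. The primary outcome and the sample size are not affected by this point.

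**What to change.** Rewrite the sentence in Statistical analyses, Process evaluation, to state:

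- a Generalized Linear Mixed Model with binomial distribution and logit link for the binary and dichotomised items. These must be written out, because Effect evaluation gives only the family ("will be done using a Generalized Linear Mixed Model") and is itself worded around change from baseline, so a cross-reference would not supply the contrast;
- a random effect for company, and one for worker where both time points are modelled;
- the strategy effect at six months adjusted for baseline, or strategy-by-time, as the reported contrast with its interval, and within-arm changes as description only;
- a simple fallback, for example a comparison of company-level proportions between strategies. With about six companies per arm and items near 100%, the logistic mixed model may meet sparse cells or fail to converge.

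The cost is about one sentence plus the fallback; the data and software are already planned. The contrast is less precise than a single-arm change: with the illustrative ±8.6 points in each arm, a difference of changes has about 8.6 × √2 = ±12.2 points. It should therefore be read as an estimate with its interval.

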#### Economic evaluation

The costs-benefit calculation for each company will be analysed descriptively on the company level. The financial costs and benefits will be given for each company.

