**Methods/Design:**

The present study is a randomised intervention trial of six months in 12 companies to establish the effects of a PE intervention guided by four face-to-face contacts (N = 6) or guided by 13 email contacts (N = 6) on the primary and secondary outcome measures at baseline and after six months. Construction companies are randomly assigned to one of the guidance strategies with the help of a computer generated randomisation table. In addition, a process evaluation for both strategies will be performed to determine reach, dose delivered, dose received, precision, competence, satisfaction and behavioural change to find possible barriers and facilitators for both strategies. A cost-benefit analysis will be performed to establish the financial consequences of both strategies. The present study is in accordance with the CONSORT statement.

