Within the review of van Eerd *et al*. [16], fifteen out of 16 studies found that the presence of a PE specialist, defined as an ergonomics consultant, was a facilitator to the PE intervention process. The role of this ergonomics consultant was firstly to initiate and then to guide the PE intervention process [16]. In this study, we want to investigate the effect of two types of guidance strategies on the use of ergonomic measures, as well as on health outcomes. In addition, we want to evaluate the process and the costs-benefits of both guidance strategies. The two guidance strategies are: 1) a face-to-face guidance strategy in which the ergonomics consultant guides the PE intervention through face-to-face contacts with the PE team; and 2) an e-guidance strategy in which the ergonomics consultant guides the PE intervention by means of e-mail contacts with the PE team.

We hypothesise that the face-to-face guidance strategy will increase the use of ergonomic measures, work ability, and physical functioning while decreasing limitations due to physical problems more when compared to the e-guidance strategy. This would be due to a higher compliance to the face-to-face guidance strategy compared with the e-guidance strategy, as a result of the presence of the ergonomics consultant within the face-to-face guidance strategy. Although the financial costs will be higher in the face-to-face guidance strategy, due to more time spent by the ergonomics consultant during the guidance sessions, more financial benefits will be gained through reduced physical risk factors due to an increase in the use of ergonomic measures.

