### Objectives

The objective of this study is to assess the effectiveness of two guidance strategies for a PE intervention: a face-to-face guidance strategy and an e-guidance strategy. The effectiveness will be assessed on 1) the primary outcome measure concerning the use of ergonomic measures by individual construction workers, and the secondary outcome measures concerning health outcomes: work ability, physical functioning and limitations due to physical problems of individual construction workers; 2) a process evaluation, and 3) a cost-benefit evaluation.

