#### Economic evaluation

A cost-benefit analysis for each participating construction company will be made. At baseline, demographic characteristics of the employees with respect to sick leave will be assessed for the construction companies. The costs of the intervention will be assessed at the end of the intervention by multiplying the time spent by the ergonomics consultant with the hourly costs. In addition, at the end of the intervention, the director of the construction companies will be asked about the costs regarding employing the ergonomic measures and additional energy and the maintenance costs of the ergonomic measures. Furthermore, the director is asked if the production per working hour changed by using the ergonomic measure.

On the benefit side, construction workers will be asked at the end of the intervention how many days they could and did use the ergonomic measure during the previous 10 working days. In addition, construction workers are asked how they judge their physical work demands compared to working without the ergonomic measure. These three questions will provide a benefit for reducing risk factors for work-related musculoskeletal disorders. Another benefit aspect will be the change in production per working hour and change in quality of the work.

With the help of the Dutch Economic Institute of the Construction Sector, the above-mentioned aspects on the company level and on the individual worker level will result in a cost-benefit analysis for each construction company.

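### The economic analysis reports each company separately and, as written, does not deliver the comparison of the two strategies that the protocol promises

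*Protocol article*

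**What the plan says.** Four places in the protocol article set the economic aim.

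- **Objectives** lists, as parts of assessing the effectiveness of the two strategies, "a process evaluation, and 3) a cost-benefit evaluation".
- **Study design** says that "The effectiveness of both guidance strategies will be compared on" a list of items that ends with "a process evaluation and a cost-benefit evaluation".
- **Abstract, Methods/Design** says: "A cost-benefit analysis will be performed to establish the financial consequences of both strategies".
- **Background** gives a direction. Face-to-face guidance is expected to cost more because it takes more of the consultant's time, yet "more financial benefits will be gained through reduced physical risk factors due to an increase in the use of ergonomic measures".

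Two places say what will be done.

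- **Outcome measures, Economic evaluation** lists the cost and benefit items. It ends with one cost-benefit analysis per company, made with help from the economic institute of the construction sector.
- **Statistical analyses, Economic evaluation** has two sentences. The first is "The costs-benefit calculation for each company will be analysed descriptively on the company level". The second adds only that financial costs and benefits will be shown company by company.

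**The concern.** The economic question, as posed, is a contrast between two randomised strategies: is the extra cost of face-to-face guidance matched by extra benefit? The planned output is 12 company results. Nothing says that they will be grouped by strategy, put on a stated common scale, summarised or contrasted.

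If the plan is followed literally, the report can describe each company's finances but does not test or estimate the hypothesis in Background. If the authors then draw a comparison anyway, they will choose the scale and the summary after seeing 12 results. That is a weak basis for a hypothesis whose direction was stated in advance.

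**Working it through.** **Aim against analysis**

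| Element | Aim (Objectives, Study design, Background) | Statistical analyses, Economic evaluation |
|---|---|---|
| Unit of interest | guidance strategy | company |
| Contrast | face-to-face against e-guidance | none stated |
| Direction | higher cost and more benefit face-to-face | not addressed |
| Summary by strategy | implied by the comparison | none stated |
| Uncertainty | not stated | none stated |

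Statistical analyses, Effect evaluation makes a useful comparison. There the worker outcomes are to be presented for the two strategies, by company. Grouping by strategy is therefore written down for the effect outcomes and absent for the economic ones.

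**What a comparison could show**

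The article gives no target or precision for the economic evaluation, so there is no economic figure to reproduce. The number of companies comes from Sample size, and it reproduces:

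- design effect = 1 + (25 − 1) × 0.01 = 1.24
- 113 × 1.24 = 140.1 workers per group
- 140.1 / 25 = 5.6, so 6 companies per group and 12 in all.

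Randomisation assigns companies in blocks of two within occupation, the second company going to the other strategy. The natural analysis is therefore paired. No standard deviation for costs or benefits is given, so precision is expressed in SD units.

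*Six complete pairs (assumption).* Let SD_d be the standard deviation of the within-pair differences, with 5 degrees of freedom.

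- 95% half-width = t(0.975; 5) × SD_d / √6 = 2.571 / 2.449 × SD_d = 1.05 SD_d
- If pairing removes no variance, SD_d = √2 × the between-company SD, and the half-width is 1.05 × 1.414 = 1.48 between-company SD.
- Possible allocations: 2^6 = 64. Smallest two-sided permutation p = 2/64 = 0.031.

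*Five complete pairs (assumption).* Limitations concedes that an occupation may contribute an odd number of companies. With only five usable pairs:

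- half-width = t(0.975; 4) × SD_d / √5 = 2.776 / 2.236 × SD_d = 1.24 SD_d
- smallest two-sided p = 2/2^5 = 2/32 = 0.063.

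*Unpaired, for reference only.* With six against six companies:

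- half-width = t(0.975; 10) × √(2/6) = 2.228 × 0.577 = 1.29 between-company SD
- a two-sided t-test at 0.05 has 80% power only for a difference of about 1.8 between-company SD, and power of about 0.35 at 1.0 SD.

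A contrast can therefore be estimated, but only large differences would stand out.

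**The case against.** The strongest reply is that Economic evaluation fixes the unit of analysis and does not forbid sorting the 12 results by strategy. Every company belongs to one randomised group, the Abstract speaks of consequences for both strategies, and table layout is something a condensed article may leave to a fuller document. Six companies per group also cannot support a formal test of any ordinary difference, so descriptive reporting is sensible. Finally, Discussion ties roll-out to increased use of ergonomic measures and not to the economic result.

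Most of this stands. Description is not the fault, and grouping the results later is possible. What does not stand is that the matter is only detail left out. The section is not silent: it names the unit and the output, and that output falls short of what Study design says will be compared.

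Four stronger readings are tempting, and the article does not support them.

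- *The economic question cannot be answered at all.* It can be approached by sorting the results by strategy; the plan simply does not say so.
- *Company totals will mainly reflect company size.* Setting only caps companies below 50 employees. A guidance cost that is much the same for each company does not grow with size in total; it varies with size only per worker. Several benefit items are already free of size, such as production per working hour and days of use out of ten.
- *Sick leave should be measured again.* The article says: "At baseline, demographic characteristics of the employees with respect to sick leave will be assessed for the construction companies". It does not list sick leave among the benefits, and Strengths expects no change in musculoskeletal disorders during the study. Leaving it at baseline contradicts nothing.
- *An exact test over all splits of 12 companies could reach a very small p-value.* That ignores the allocation in pairs.

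**Conclusion.** The point holds as a mismatch between aim and analysis. Objectives and Study design include the cost-benefit evaluation in the comparison of strategies, and Background gives it a direction. The two economic sections plan only a descriptive result for each company, so the comparison is not delivered as written.

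Its weight is modest. The primary outcome, its sample size and its model are untouched, and a cheap change cures it. A contrast would be imprecise: about ±1.05 SD_d with six complete pairs, and about ±1.24 SD_d with five. These figures assume that 12 companies are recruited as planned, that pairs are complete as stated, and that company-level differences are roughly normal. Their size in money cannot be given, because the article states no variability for costs or benefits.

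**What to change.** Amend Statistical analyses, Economic evaluation as follows.

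1. Report each company's costs, benefits and net result on a common scale, for example per worker over one common period, with the totals alongside. Fix the scale before results are seen, in agreement with the economic institute.
2. Group the 12 results by randomised strategy and mark the occupation pair.
3. Give the between-strategy difference with a 95% interval on company-level values, respecting the pairing, and state how a company without a partner is handled.
4. Label the result as exploratory estimation. If an exact p-value is shown, base it on the paired allocations.

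The cost is one table and a few sentences, with no need for extra data collection. The downside is a wide interval that must be reported openly.

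If the authors do not want a comparison, the alternative is to reword Study design and the economic hypothesis in Background, and to align Objectives, so that they promise only a company-by-company financial description. That costs nothing in analysis but gives up the between-strategy economic aim.
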